### 10.12 TRIAL MONITORING AND AUDITING

#### 10.12.1 Trial monitoring

Study conduct will be monitored by independent monitors. External clinical trial monitoring visits are provided by the sponsor at trial initiation, and then after approximately 10-20% of patients have been recruited, and then regularly (at least yearly) thereafter and at trial closeout, or more frequently if so required; e.g. if the fieldwork is about 18 months, this means that each site is visited approximately four times by external monitors. The results from each monitoring visit will help inform whether more frequent or earlier repeat visits are required.

Because of the existing international travel restrictions, the independent monitors will likely be recruited from local academic or commercial Contract Research Organisations (CROs) in-country. This will take place by visiting the participating clinical research sites. However, this can also take place remotely if on-site monitoring is not possible due to local social distancing restriction on travel and movement of people are in place, in which it will take place by teleconference calls and provision of electronic and photographic evidence of documentation and infrastructure.

Monitors will review the individual participant records, including consent forms, case report forms, supporting data, laboratory specimen records, and endpoints through laboratory and medical records (physicians' progress notes, nurses' notes, individuals' hospital charts), to ensure the protection of study participants, compliance with the protocol, and accuracy and completeness of records. The monitors also will inspect the sites' trial site and master files to ensure that requirements are being followed and the sites' pharmacies to review product storage and management.

#### **10.12.2 Auditing**

The independent clinical monitoring process will be audited by a study staff from the sponsor's research office at LSTM in Liverpool, and LSHTM in London, UK.

#### **10.12.3 Role of sponsor**

The sponsor reserves the right to suspend temporarily or prematurely discontinue this study at any time for reasons including, but not limited to, safety or ethical issues or severe non-compliance. If the sponsor determines such action is needed, it will discuss this with the investigator. When feasible, the sponsor will provide advance notification to the investigator of the impending action prior to it taking effect. The sponsor will promptly inform the ethics committees and provide the reason for the suspension or termination.

### **10.13 OTHER QUALITY CONTROL MEASURES**

#### **10.13.1 Safety monitors**

A local paediatrician and physician will act as trial safety monitors, one per country.

#### **10.13.2 Internal monitoring**

Each of the partner's institutions has their own internal quality control teams who will conduct internal monitoring on a regular basis, and help prepare for external monitoring visits.

#### **10.13.3 Training**

The country Principal Investigators are responsible for the conduct of the study at the study sites, including delegation of specified study responsibilities, and training of study staff. The training will include instructions on the use of PPE and other infection prevention and control (IPC) measures (see section 12.7.3.1, Biohazard containment to limit risks of SARS-CoV-2 transmission, page 65). All staff involved with the consent procedures will have been trained to GCP or equivalent level.

Each site will maintain a record of all individuals involved in the study (medical, nursing and other staff) and will ensure that all persons assisting with the trial receive the appropriate training about the protocol, the investigational product(s) and their trial-related duties and functions, including formal certified GCP training. During the study, the regular spot checks will be conducted to assess the performance of the study site staff members and re-training provided where necessary.

#### 10.13.4 Quality assurance/control of laboratory tests

Regular audits of laboratory performance will be completed by experienced supervisors according to standard operating procedures already in place in the respective laboratories.

## 11 STATISTICAL CONSIDERATIONS

---

### 11.1 SAMPLE SIZE DETERMINATION

Sample size calculations were conducted with PASS v20.

#### 11.1.1 Cohort

The primary endpoint used for the sample size calculations is the cumulative proportion of patients that progresses at least one category in disease severity from enrolment to day-28 based on the WHO clinical progression scale (see 16.4, Appendix IV. WHO clinical progression scale, page 82). At least one category increase in disease severity is defined as progressing from either asymptomatic or mild disease at enrolment to at least moderate disease requiring hospital admission (excluding hospitalisations for isolation only), or from moderate disease at enrolment to severe disease, or from severe disease at enrolment to death. For definitions of each disease severity category, see 16.4, Appendix IV. WHO clinical progression scale, page 82. The sample size calculations to determine the crude impact (i.e., unadjusted for potential confounders) of malaria on COVID-19 disease regression suggests that a pooled sample size of 708 (673 completers) of whom approximately 142 are malaria positive and 566 are malaria negative (135 and 538 completers) would provide 90% power to detect a 50% difference in the primary endpoint from 30% in the malaria-negative group to 45% in the malaria positive group ( $\alpha=0.05$ , 5% loss to follow-up by day 28). The true power is likely to be lower when the confounding effect of baseline differences between malaria and non-malaria patients (such as age is considered). However, the inflation in the sample size required is difficult to estimate a priori. Similar crude sample size calculations using 80% power suggest 522 participants are required. Thus overall, a sample size of 708 participants would provide 80% power to detect a 50% difference in the primary endpoint allowing for a 35.6% inflation in sample size ( $708/522=1.356$ ) to take adjustment for confounding into account in multivariate or stratified analysis. The sample size calculation for the COVID-19 cohort study assumes that each country will recruit 354 COVID-19 participants and that approximately 20% of them are coinfecting with malaria (RDT positive), representing a weighted average of 15% of 354 COVID-19 cases in Kenya and 25% of 354 cases in Burkina Faso.

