| 
 
To determine if malaria infection affects COVID-19 disease presentation and duration
 
                                                  | 
 
Symptoms and duration of COVID-19 by day-28 in cases with and without malaria
 
                                                                                                                                                                                                                                                                                           |
| 
 
To determine if malaria infection in COVID-19 patients alters the antibody response to SARS-CoV-2 infection
 
                           | 
 
Cumulative seroconversion rates* (total antibody, IgG, IgM, IgA) by days 7, 14, 21, 28, and total antibody, IgG, IgM, IgA antibody titres against SARS-CoV-2 by day-28 expressed as the geometric mean, maximum, and change from baseline
 
Seroreversion rates for IgG, IgM, IgA and geometric mean antibody titres against SARS-CoV-2 by month 3, 6 and 12
 
     |
| 
 
To determine if malaria infection in COVID-19 alters the inflammatory, genomic, and cellular immune responses to SARS-CoV-2 infection
 
 | 
 
Multiplex serum cytokine markers; Transcriptional profiling (gene expression) of whole blood; Fixed whole blood for T and B cell markers by day-28
 
                                                                                                                                                                                                                      |
| 
 
To determine if malaria infection in COVID-19 alters the viral load or duration of SARS-CoV-2 infection
 
                               | 
 
Median viral load of SARS-CoV-2 detected from mid-nasal swabs by PCR
 
Cumulative incidence of SARS-CoV-2 clearance (defined as the proportion of participants with negative nasal swabs) by days 7, 14, 21 and 28
 
Time to clearance of nasal SARS-CoV-2, defined as negative SARS-CoV-2 RNA PCR tests (swabs collected on days 1, 3, 7, 14, 21 and 28)
 
 |

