| 
 
To determine if treatment of malaria infection with pyronaridine-artesunate in COVID-19 alters the inflammatory, genomic, and cellular immune responses to SARS-CoV-2 infection compared to treatment with artemether-lumefantrine
 
 | 
 
Multiplex serum cytokine markers; Transcriptional profiling (gene expression) of whole blood; Fixed whole blood for T and B cell markers by day-28
 
                                                                                                                                                                                                                   |
| 
 
To compare the clinical and parasitological efficacy of pyronaridine-artesunate versus AL in COVID-19 patient coinfecting with malaria parasites.
 
                                                                                  | 
 
The proportion with early treatment failure, late clinical failure, late parasitological failure or an adequate clinical and parasitological response. Recrudescence will be differentiated from new infection by genotyping of malaria parasites by day 42
 
                                                                                                          |
| 
 
To determine if pyronaridine-artesunate compared to artemether-lumefantrine alters COVID-19 disease progression and severity
 
                                                                                                       | 
 
COVID-19 symptoms, duration and severity as defined by a severity index score by day 28
 
The proportion of days with a fever after randomization
 
The proportion of days with respiratory symptoms after randomization
 
                                                                                                                               |

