#### 7.2.1.1 Adverse events

Artemether-lumefantrine has a wide therapeutic index and is generally well-tolerated, with reported side-effect such as nausea, dizziness and headache that are not easily distinguishable from symptoms of acute malaria. Artemether-lumefantrine does not significantly prolong the QTC interval.

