## 16.4 APPENDIX IV. WHO clinical progression scale

Figure 6: WHO clinical progression scale

| Patient State                  | Descriptor                                                                             | Score |
|--------------------------------|----------------------------------------------------------------------------------------|-------|
| Uninfected                     | Uninfected; no viral RNA detected                                                      | 0     |
| Ambulatory mild disease        | Asymptomatic; viral RNA detected                                                       | 1     |
|                                | Symptomatic; independent                                                               | 2     |
|                                | Symptomatic; assistance needed                                                         | 3     |
| Hospitalised: moderate disease | Hospitalised; no oxygen therapy*                                                       | 4     |
|                                | Hospitalised; oxygen by mask or nasal prongs                                           | 5     |
| Hospitalised: severe diseases  | Hospitalised; oxygen by NIV or high flow                                               | 6     |
|                                | Intubation and mechanical ventilation, $pO_2/FiO_2 \geq 150$ or $SpO_2/FiO_2 \geq 200$ | 7     |
|                                | Mechanical ventilation $pO_2/FiO_2 < 150$ ( $SpO_2/FiO_2 < 200$ ) or vasopressors      | 8     |
|                                | Mechanical ventilation $pO_2/FiO_2 < 150$ and vasopressors, dialysis, or ECMO          | 9     |
| Dead                           | Dead                                                                                   | 10    |

ECMO=extracorporeal membrane oxygenation.  $FiO_2$ =fraction of inspired oxygen. NIV=non-invasive ventilation.  $pO_2$ =partial pressure of oxygen.  $SpO_2$ =oxygen saturation. \*If hospitalised for isolation only, record status as for ambulatory patient.

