Pyramax was demonstrated in Phase III clinical studies in both the Per Protocol (PP) and Intent to Treat (ITT) populations to be non-inferior to artemether-lumefantrine and mefloquine + artesunate in the treatment of acute uncomplicated *P. falciparum* in 2280 children and adults for the primary endpoint of polymerase chain reaction (PCR)-adjusted adequate clinical and parasitological response (ACPR) at 28 days. In addition, Pyramax was also found to be non-inferior to the comparator agents for the secondary endpoints of parasite PCR-adjusted ACPR at 42 days. Pyramax was rapidly effective, with more than 90% of subjects clearing parasites and fever within 48 hours. Parasite count (*P. falciparum* asexual forms) decreased rapidly (during the first 16 hours) in both the Pyramax and comparator groups. Time to parasite clearance was statistically significantly shorter in the Pyramax group compared with artemether-lumefantrine group based on the log-rank test. In the integrated analysis of all Phase III studies with *P. falciparum*, no clinically important differences in PCR-adjusted ACPR were observed by region, age, gender, race, weight, previous malaria episode, baseline parasitaemia, or formulation. Crude cure rate results were also similar. The median time to fever clearance was 15.5 hours.

In all studies conducted in *P. falciparum* malaria, there was a marginal but consistently longer gametocytes clearance time in the Pyramax groups as compared to mefloquine plus artesunate or artemether-lumefantrine groups. Further trials are awaited to address the mosquito infectivity.

In an analysis of a repeat-dose longitudinal study of 1342 patients treated with Pyramax tablets and granules for oral suspension, examining safety and efficacy of repeat dosing; of the 770 patients weighing  $\geq 20$  kg, 434 (56.4%) received at least one further treatment and 31.6% had a second or more re-treatment. Reasons for non-inclusion into the study or non re-treatment were complicated malaria or hyperparasitaemia or significantly raised liver enzymes as well as comorbidities such as HIV, hepatitis, or severe malnutrition. Efficacy findings were similar to those in pivotal trials and were maintained with repeated treatment episodes. Patients previously excluded or poorly represented in the clinical studies will be included in a pharmacovigilance study being conducted in endemic areas.

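### The cohort primary endpoint scores any non-isolation admission as COVID-19 progression, so admissions caused by malaria can count almost only in the malaria-positive group

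*Protocol*

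**What the plan says.** The cohort's primary objective is to learn whether malaria infection affects COVID-19 severity (section 4.2). Section 11.1.1 makes this operational as "the cumulative proportion of patients that progresses at least one category in disease severity from enrolment to day-28", using the WHO clinical progression scale. One way to meet it is to progress "from either asymptomatic or mild disease at enrolment to at least moderate disease requiring hospital admission (excluding hospitalisations for isolation only").

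Appendix IV (section 16.4) carries the same single exclusion: "If hospitalised for isolation only, record status as for ambulatory patient". In that scale moderate disease begins at score 4, hospitalised without oxygen. Neither place asks whether COVID-19 was the reason for admission, and the protocol contains no adjudication rule.

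Section 4.2 also lists as a secondary cohort endpoint "Symptoms and duration of COVID-19 by day-28 in cases with and without malaria".

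**The concern.** The exposure is itself an illness that can put a person in hospital. A malaria-positive participant with silent SARS-CoV-2 infection who is admitted for malaria, without oxygen, meets the primary endpoint. The protocol foresees such routes:

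- Section 7.4.3.2 permits treatment for severe malaria.
- Section 9.2.7 provides for recurrent malaria on days 7 to 42.
- Section 10.10.2 sends adverse events of the study drugs to hospital for evaluation, and only malaria-positive participants receive those drugs at enrolment.
- Section 7.1.1.1 says that confirmed symptomatic cases in Kenya are admitted for supportive management, so becoming ill from malaria may turn an ambulatory case into a scored admission.

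Malaria-negative participants have little of this risk. This is outcome misclassification produced by the exposure, not confounding, so the adjusted models of section 11.2.4.1 do not deal with it. A positive primary result would be hard to separate from the fact that people with malaria are sometimes admitted for malaria.

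The symptom endpoint has a milder form of the same difficulty if FLU-PRO is used. Of the 34 items in Appendix V (nose 5, throat 4, eyes 3, chest 7, gastrointestinal 4, body/systemic 11), 15 are gastrointestinal or body/systemic. Many of these, such as chills, headache, body aches and feeling hot, also occur in malaria. The protocol itself describes artemether-lumefantrine as having "reported side-effect such as nausea, dizziness and headache that are not easily distinguishable from symptoms of acute malaria".

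**Working it through.** **Inputs (section 11.1.1; two-sided testing from 11.2.1).** Event rates are 30% malaria-negative and 45% malaria-positive, with 538 and 135 completers and alpha 0.05. The stated power is 90%.

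**Reproducing the plan.** Two-proportion z-test, pooled variance under the null:

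- pooled p = (538×0.30 + 135×0.45)/673 = 0.330
- SE under the null = √[0.330×0.670×(1/538 + 1/135)] = 0.0453
- SE under the alternative = √[0.30×0.70/538 + 0.45×0.55/135] = 0.0472
- (0.15 − 1.96×0.0453)/0.0472 = 1.30, so power is 90.3%

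The same method gives about 703 to 705 participants at 90% power (stated 708) and 521 at 80% (stated 522). The plan's arithmetic is sound; the issue is what the endpoint counts.

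**Effect of malaria-only admissions.** Assume malaria has no effect on COVID-19, so true progression is p = 0.30 in both groups. Let m be the probability that a malaria-positive participant who would not otherwise progress is admitted for malaria alone. The documents give no value for m, so a range is shown.

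Observed rate in the malaria-positive group = p + (1 − p)m. The false-positive risk is the probability that the same test rejects in either direction.

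| m (assumed) | Spurious admissions, 135×0.70×m | Observed rate | Apparent RR | False-positive risk |
|---|---|---|---|---|
| 2% | 1.9 | 31.4% | 1.05 | 6.3% |
| 5% | 4.7 | 33.5% | 1.12 | 12.8% |
| 10% | 9.5 | 37.0% | 1.23 | 35.2% |

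For m = 5%: pooled p = 0.307, the two SEs are 0.0444 and 0.0452, and (0.035 − 1.96×0.0444)/0.0452 = −1.15. The upper tail is 12.5% and the lower tail 0.3%.

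**Two reference points.** With 30% observed in the malaria-negative group, an observed excess of 8.8 points, about 12 of 135 patients, reaches significance (0.088/0.0448 = 1.96). To mimic the full design effect of 45%, m would have to be 0.15/0.70 = 21.4%, about 20 of the 94.5 malaria-positive completers who would not otherwise progress.

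**If progression is rarer than planned.** At an assumed 10% event rate, which is not the protocol's figure, the same m of 2%, 5% and 10% gives RRs of 1.18, 1.45 and 1.90 and false-positive risks of 10.5%, 34% and 79%.

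**The case against.** Several features keep the bias down or push it the other way, and they stand.

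- Nested-trial participants must have uncomplicated malaria and mild disease. Need for parenteral treatment excludes them, and treatment starts the same day (sections 6.2.3 and 9.2.1.3). This points to a low m, and at 2% the false-positive risk is close to nominal. The parenteral-treatment exclusion is not repeated for the cohort (6.2.2.2).
- Asymptomatic and mild disease are merged, so ambulatory malaria symptoms do not move the primary endpoint.
- A patient already admitted for malaria at enrolment starts as moderate and must become severe to count.
- Clinical scales, FLU-PRO included, are analysed as change from enrolment (11.2.4.2). Malaria symptoms that resolve would make the malaria-positive group look better.
- Malaria acquired during follow-up by malaria-negative participants pulls towards the null.
- FLU-PRO is only an alternative instrument (10.3.1), and Appendix V says it can be scored by domain.

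The direct remedy, rescoring malaria-attributed admissions as ambulatory within the primary endpoint, has a real fault. Staff who know malaria status would remove events almost only from the exposed group, and might delete indirect effects that the first null hypothesis in section 3.3 expressly covers.

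A reader might also infer that the nested trial's endpoint "The proportion of days with a fever after randomization" makes malaria look harmful. It cannot, because both randomised arms have malaria. At most it mixes antimalarial with antiviral effects. The appended product information states "Time to parasite clearance was statistically significantly shorter in the Pyramax group compared with artemether-lumefantrine group"; it reports no difference in fever clearance between the two drugs. The trial's primary question rests on Day 7 viral clearance read by blinded laboratory staff (4.3 and 7.4).

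None of this supplies a way to tell, from the primary endpoint alone, a score-4 admission for malaria from one for COVID-19.

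**Conclusion.** The definition that the protocol fixes allows malaria-caused admissions to score as COVID-19 progression, almost only in the malaria-positive group, and confounder adjustment will not correct it. The likely direction is apparent harm. The size is unknown: over assumed malaria-only admission risks of 2% to 10%, at the planned 30% event rate and no true effect, the spurious RR runs from 1.05 to 1.23 and the false-positive risk from 6% to 35%. The calculation assumes independent malaria admissions and none of the counteracting mechanisms above.

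A reader might conclude that malaria will certainly appear to worsen COVID-19. The documents do not support that, because they give no admission rate, the entry and scoring rules limit the bias, and some mechanisms act in reverse. This should be fixed, but it does not require a new primary endpoint.

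**What to change.** Keep the primary endpoint as defined. Then:

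1. In sections 11.1.1 and 11.2.4.1, prespecify a supportive analysis of progression to score 5 or above (oxygen or more) or death, among participants below score 5 at enrolment. It needs no judgement about cause.
2. State in advance that a malaria effect seen only through score-4 admissions will not be read as an effect on COVID-19 severity.
3. Tabulate the recorded reason for admission by malaria status. Applying the isolation exclusion already requires a reason to be known.
4. If FLU-PRO is used for the cohort symptom endpoint, report the respiratory domains (nose, throat, chest) and the gastrointestinal and body/systemic domains separately by malaria status.

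The cost is a few sentences of endpoint and analysis wording, largely on data already collected; care does not change. The supportive analysis will have fewer events and less precision, and oxygen use is not fully specific to COVID-19. The wording should be fixed before outcomes are examined by malaria status, because a rule added later would look driven by the result.
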